### Outcome measures

To measure objectively the healing of the gluteus medius and to check the positions of the components of the joint prosthesis, MRI and plain radiographs will be taken 3 and 12 months postoperatively. At the same control visits, a trained physiotherapist will measure the hip strengths and the OHS will be recorded. Clinical examinations will be conducted (movements of both hip joints, wound healing) and any limping or a positive Trendelenburg sign will be recorded.

### Oxford hip score

Patients will fill OHS forms preoperatively and postoperatively at 3 and 12 months after surgery.

### Magnetic resonance imaging - MRI

MRI sequences will be used according to the MARS protocol (Pfirrmann et al. 2005), where T1 sequences will be used to identify gluteus medius pathology, and coronal and sagittal images are taken. The imaging time per sequence is about 3–6 min and the entire MRI study will take approximately 30 min in total.

### Clinical examination – gait and Trendelenburg test

The Trendelenburg test and the hip lag sign will be examined 3 and 12 months after the THA by the surgeon. The hip lag sign is tested by putting the patient or his side with the operated hip upwards and by asking the patient to abduct the examined extremity. This testing position mimics the validated hip strength measurements used in the present study protocol and is shown below.

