### Study design

The study is a multicenter RCT with parallel study groups (1:1). The study design is double blinded where neither the orthopedic surgeon nor the patient know whether the patient receives PRP treatment or placebo. The flowchart of the study cohort is shown in Fig. 1 including enrollment, allocation, follow-up and analysis. After having provided written informed consent the patients are enrolled. They participate voluntary in the study, they may withdraw from the trial at any time and are not compelled to explain the reason for withdrawal.

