**Fig. 1 Fig1:**
[figure not shown]
Flowchart of the trial: enrollment, treatment allocation and follow-up scheme

Enrollment began with a pilot phase conducted in a secondary hospital in Finland, where the study protocol was followed. A total of 18 patients were recruited. The THA procedures was done by four orthopedic surgeons experienced in the Hardinge approach and in injecting PRP during closure. Postoperative open care visits to the same orthopedic surgeons who performed the THA were carried out and hip strength assessments were done by a trained physiotherapist.

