### Randomisation and concealment

The final decision of inclusion or exclusion of the patient into the trial will be done during the THA procedure where the surgeon will evaluate the condition of the gluteus medius. If the gluteus medius seems abnormal (i.e., torn or atrophied), the patient will be withdrawn from the study. If gluteus medius is intact, the surgeon will notify the staff nurse who will open a sealed envelope. The sealed envelopes will be kept in a secure and agreed location known only to the trial physicians and nurses; the surgeon will not know which group the participant is included. If the patient is allocated to receive placebo, 50 ml of blood will be drawn but the blood will not be prepared for PRP. The venous sample will be taken and PRP prepared by a study physician (AA or JK) who will not participate the THA surgery. Instead, after about 30 min the surgeon will be given a blinded (taped) 10 ml syringe with saline by the instrument nurse.

If the patient is randomized to receive PRP, 50 ml of blood is drawn, as for the placebo procedure. This blood will be prepared in an operation room behind the surgeons back. Then the surgeon will be given a blinded (taped) 10 ml syringe with PRP.

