## Discussion

The present study protocol uses has several point-of-care methods in an attempt to reveal if a single perioperative PRP injection into the reinsertion site of the gluteus medius during THA benefits the patient. Firstly, we will analyze MR images to examine the anatomy and healing of the reattached gluteus medius. MRI is of high clinical value in symptomatic THA patients who have a compromised gluteus medius muscle (Pfirrmann et al. 2005). MRI can also reveal significant abductor atrophy after THA (Engelken et al. 2014; Roth et al. 2014). Secondly, OHS data will be collected for a detailed understanding of the overall patient outcome after THA. Previously OHS has been compared to various hip scores and it has been validated as a registry tool (Nilsdotter et al. 2001). It has been shown that a change in the total score of 4.85 is clinically meaningful (Beard et al. 2015). Thirdly, clinical examination with special attention to any gait abnormalities will be included. Historically, the Trendelenburg sign has been used to diagnose gluteus medius injuries, but the reliability of this sign has been questioned (Youdas et al. 2010). Poor abduction strength seems to be associated with abnormal gait (limping). During gait, abduction of the lower extremity is produced by the gluteus medius muscle (Anderson et al. 2003). Kaltenborn et al. have created a clinical sign – the hip lag sign – which correlates with the degree of gluteus medius impairment in MRI (Kaltenborn et al. 2014). The reported specificity and sensitivity of the hip lag sign is excellent, 96.5% and 89.7%, respectively. In the present study the hip lag test will be carried out augmented by dynamometric measurements to assess the strength of the hip postoperatively. This method has been validated for hip abduction power measurements (Widler et al. 2009).

The need for THA will increase massively in the future and research to identify more rapid and cost-effective postoperative rehabilitation is needed. The present study plan describes a RCT aimed at determining if PRP benefits a given subgroup of THA patients.

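### The surgeon, the follow-up rater most exposed to unblinding cues, rates the Trendelenburg test and hip lag sign; a physiotherapist already at those visits could do it

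*Protocol article*

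**What the plan says.** The section on clinical examination (gait and Trendelenburg test) names the rater: "The Trendelenburg test and the hip lag sign will be examined 3 and 12 months after the THA by the surgeon". Outcome measures describes another assessor at the same 3- and 12-month visits: "At the same control visits, a trained physiotherapist will measure the hip strengths and the OHS will be recorded".

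On who the surgeon is, Study design reports that the pilot followed the study protocol and that "Postoperative open care visits to the same orthopedic surgeons who performed the THA were carried out". In Interventions and in Randomisation and concealment, the surgeon is the person who operates and is handed the syringe.

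On blinding, Study design declares that "neither the orthopedic surgeon nor the patient know whether the patient receives PRP treatment or placebo". Randomisation and concealment describes the means. For placebo, "50 ml of blood will be drawn but the blood will not be prepared for PRP", and a taped saline syringe is handed over after about 30 minutes. For PRP, "This blood will be prepared in an operation room behind the surgeons back", followed by "Then the surgeon will be given a blinded (taped) 10 ml syringe with PRP".

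On the signs themselves, Objectives and study hypothesis places clinical signs under the secondary objective. The Discussion says that "the Trendelenburg sign has been used to diagnose gluteus medius injuries, but the reliability of this sign has been questioned", and reports high specificity and sensitivity for the hip lag sign (96.5% and 89.7%).

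**The concern.** Both signs depend on an examiner's judgement. The person who makes that judgement stood in the operating room after the envelope was opened, injected the syringe contents, and is looking at the result of their own tendon repair. Among those who assess the patient at follow-up, nobody described in the article has had more opportunity to guess the arm.

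If the surgeon does guess the arm and the guess colours borderline ratings, the trial could report a PRP effect on these signs that reflects the rater and not the tendon. The article stresses objective follow-up of gluteus medius healing, so giving the judgement-dependent signs to the most exposed rater works against its own aim.

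**Working it through.** **1. Who rates.** The clinical examination section says only the surgeon, not the operating surgeon. Two things support the narrower reading: the pilot, run under the study protocol, sent patients back to whoever had operated on them, and the surrounding sections use the term for the person operating. No other rater is named for these two signs. The reading is an inference, but the most likely one. Limping is to be recorded at the visits, with no rater named.

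**2. What could unblind this person.**

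| | PRP arm | Placebo arm |
|---|---|---|
| Blood drawn | 50 ml | 50 ml |
| Blood processed | yes, in an operation room behind the surgeon | no |
| Sham processing | not applicable | none described |
| Syringe | taped, 10 ml | taped, 10 ml, after about 30 min |

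The draw and the syringe are matched between arms. The processing is not, and it takes place near the surgeon.

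**3. Which outcomes are exposed.** The OHS is completed by the patient, strength is measured by the physiotherapist, and MRI is a separate examination. The sample size rests on the OHS: a 5-point difference, SD 7.8, alpha 0.05 (two-sided assumed), 80% power. By the normal approximation, n = 2 × (1.96 + 0.8416)² × 7.8² / 5² = 38.2, so 39 per group. The exact t calculation gives 39.19, so 40 per group, which is the article's figure. Changing who rates the two signs does not touch it.

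**4. Illustration of the size.** Inputs:
- n = 45 per arm, from the 90 patients in the Abstract allocated 1:1.
- True positive rate p, the same in both arms. The article gives no design rate. The Background reports the occurrence of a positive Trendelenburg sign and abnormal gait as at least 11%. The range 11% to 50% is assumed.
- Shading d in each direction (ratings lowered by d under PRP, raised by d under placebo), assumed 2 to 5 percentage points, with the rater's guess always right.

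Formulas: SE = √(2p(1 − p)/45); z = 2d/SE; false-positive rate = P(Z > 1.96 − z) + P(Z < −1.96 − z).

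Example, p = 0.30 and d = 0.05: SE = √(2 × 0.3 × 0.7/45) = 0.0966; z = 0.10/0.0966 = 1.035; rate = 0.178 + 0.001 = 0.179.

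| p | SE | d = 2 points | d = 3 points | d = 5 points |
|---|---|---|---|---|
| 11% | 0.0660 | 9% | 15% | 33% |
| 20% | 0.0843 | 8% | 11% | 22% |
| 30% | 0.0966 | 7% | 10% | 18% |
| 50% | 0.1054 | 7% | 9% | 16% |

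Without shading each cell would be 5%.

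**5. How soft these figures are.** At p = 11%, 5 points each way means 6% against 16%, which is heavy shading. If shading is instead proportional, one sixth of the rate each way, the gap at 11% is 3.7 points, z = 0.0367/0.0660 = 0.556, and the false-positive rate is about 9%. If the surgeon guesses correctly only three times in four, the net gap halves (0.75 − 0.25 = 0.5). At p = 30% and d = 5 points, z is then 0.518 and the rate about 8%.

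**The case against.** The strongest answer is that the surgeon is declared blinded and that the article takes real steps to achieve it: blood is drawn in both arms, both syringes are taped, saline is held back for about 30 minutes, and a study physician outside the surgery prepares the PRP. That stands. A reader might infer that the plan uses an unblinded assessor; the documents do not support this. The risk arises only if blinding fails.

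A reader might also infer that the injected fluid gives the arm away at the wound. The article says nothing about how the fluid looks. Injection follows closure of the tendon over bone tunnels, and no leakage is expected. The documented cue is the processing difference, and that could be repaired at its source. If it were, this point would shrink. The rater would still have given the injection and would still be judging their own repair.

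Nor does the article call the Trendelenburg sign unreliable. It says that reliability has been questioned, rates the hip lag sign highly, and supplements it with dynamometry.

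Finally, the physiotherapist is not shown to be better blinded. Only the surgeon and the patient are named as blinded, and nothing says that the physiotherapist stays out of the operating room. This stands, and the change has to settle it.

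**Conclusion.** The point holds as a design weakness of limited reach. The article assigns two examiner-judged signs to the follow-up rater with the most exposure to unblinding cues, although another trained assessor is present at the same visits. The conclusion rests on reading the surgeon as the operating surgeon, and on the possibility, not the certainty, that blinding fails.

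Under the assumed inputs the false-positive rate for these comparisons would be roughly 7% to 33% instead of 5%. The lower part of that range is the more plausible if shading is proportional or guesses are imperfect. No single value should be quoted as an estimate. A reader might infer that the main result is compromised; it is not, because the OHS, dynamometry and MRI are not described as surgeon-rated. The change is worth making because it is cheap.

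**What to change.** In the clinical examination section, have the physiotherapist who already attends at 3 and 12 months rate and record the Trendelenburg test, the hip lag sign and limping as the trial outcome. This should come before the dynamometry, so that the strength reading does not influence the rating, and before the surgeon sees the patient. State that this person takes no part in the operation or the PRP preparation and has no access to the allocation or the operation note. The surgeon's examination continues for clinical care.

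The cost is a few minutes per visit and brief training on the signs. The hip lag position already resembles the side-lying strength test. No additional visit, staff or patients are needed.

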### Hip strength measurements

To test the reattachment and function of the detached gluteus medius required by the Hardinge approach, hip abduction strength will be measured with a dynamometer. The abduction forces of both lower extremities will be tested with the patient lying supine and on his side (Fig. 3).

**Fig. 3 Fig3:**
[figure not shown]
Dynamometric hip strength measurement (Widler et al. 2009)

### Reoperations, loss to follow-up and missing data

All reoperations, loss to follow-up and missing data will be recorded. Patients who experience perioperative or postoperative complications related to healing of the gluteus medius (i.e.*,* trochanteric fracture or infection) will be censored from the final analysis. In order to minimize loss to follow-up and missing data, the dates for the postoperative visists will be set and given in writing to the patients already at the ward; this includes the visit for strength assessment and clinical examinations. MRI and radiography will be done during the same week as the 3- and 12-month clinical control visits.

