## Methods and analysis

### Objectives and study hypothesis

The objective of this trial is to compare the healing of the gluteus medius insertion among patients who have undergone THA. We will operate patients through the Hardinge approach and inject PRP or placebo in the region of the gluteus medius tendon insertion. The primary objective is to investigate the healing of the gluteus medius insertion objectively with MRI (anatomy) and hip strength measurements (dynamometer). The secondary objective is to record and analyze the changes in the Oxford Hip Score (OHS) by comparing the OHS before and after surgery and to record and analyze clinical signs, especially limping, pain and movement restrictions. The tertiary objective is to analyze safety and the cost-effectiveness of PRP in THA. The hypothesis is that PRP facilitates postoperative healing of the gluteus medius among elderly patients after THA and that the healing can be verified objectively seen by MRI and dynamometry.

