### Data management and statistical analysis (sample size)

Due to multiple outcome settings, the OHS was used as the primary outcome measure and power calculations were carried out accordingly. Thus, a sample size of 40 patients per intervention group has been calculated as being sufficient when a 5 point mean difference (SD 7.8 point) is used to identify a significant difference at a significance level of 0.05 and 80% power (two-sample t-test).

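### The protocol removes patients with trochanteric fracture or infection from the final analysis, although postoperative events follow randomisation and lie on the healing pathway under test

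*Protocol article*

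**What the plan says.** The rule is in the protocol article under *Reoperations, loss to follow-up and missing data*. "Patients who experience perioperative or postoperative complications related to healing of the gluteus medius", with two examples, "trochanteric fracture or infection) will be censored from the final analysis". The same paragraph also states: "All reoperations, loss to follow-up and missing data will be recorded".

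Four other places bear on it:

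- *Randomisation and concealment* places allocation inside the operation: "If gluteus medius is intact, the surgeon will notify the staff nurse who will open a sealed envelope". *Interventions* places the injection later still, after the tendon has been sutured back.
- *Objectives and study hypothesis* names the target: "The primary objective is to investigate the healing of the gluteus medius insertion objectively with MRI (anatomy) and hip strength measurements (dynamometer". It adds a third tier: "The tertiary objective is to analyze safety and the cost-effectiveness of PRP in THA".
- *Data management and statistical analysis (sample size)* says that "the OHS was used as the primary outcome measure and power calculations were carried out accordingly", with a two-sample t-test.
- *Outcome measures* covers the 3- and 12-month visits: "Clinical examinations will be conducted (movements of both hip joints, wound healing" appears there, alongside MRI, radiographs, strength and OHS.

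**The concern.** A randomised comparison is protected only while the groups analysed are those formed by the envelope. This rule takes patients out because of something that happens later, and it picks them by whether the complication bears on healing of the tendon that was injected. Removal can therefore depend on the treatment and on the outcome together.

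If PRP prevents such complications, the rule discards the placebo patients who would have shown the benefit. If PRP, or the injection of it, promotes infection, the rule discards the PRP patients who would have shown the harm. Neither direction can be ruled out beforehand. Every efficacy outcome is affected. Because safety is a stated objective and no exemption is given, the comparison of fracture and infection between arms is also exposed.

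**Working it through.** **1. The plan's own sample size.** Inputs from the sample-size section: difference 5, SD 7.8, alpha 0.05 (two-sided assumed, since a one-sided test would need only 31), power 80%.

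- Normal approximation: n = 2 × (1.960 + 0.842)² × 7.8² / 5² = 38.2, so 39 per group.
- Exact two-sample t-test: 39.2, so 40 per group. The stated 40 reproduces.
- t-test power is 80.8% at 40 per group and 85.3% at 45 per group (the planned 90, split 1:1).

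The stated sample size is not at fault.

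**2. What censoring can mean here.** OHS, strength and MRI findings are recorded at fixed visits, and the planned test compares two means. No time-to-event analysis is described, so a censored patient is one left out.

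**3. Which events come after allocation, and which can depend on PRP.**

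| Event | Relative to envelope | Can PRP affect it? | Effect of removing it |
|---|---|---|---|
| Abnormal muscle or fracture found before opening | Before | No | None; not randomised |
| Intraoperative event after opening, before injection | After | No | Loss of precision, no expected bias |
| Postoperative fracture or infection | After | Possibly | Possible bias, either direction |

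The rule treats all perioperative and postoperative events alike. The third row is the problem.

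**4. Size on the OHS (illustration only).** The documents give no fracture or infection rate and no OHS value for such patients. Assume 45 per arm and a deficit D of 10 to 20 points in removed patients. The target is the difference in all randomised patients.

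Distortion = (excess removed in one arm / 45) × D

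| Removed (one arm vs the other) | D = 10 | D = 20 | Share of 5 points |
|---|---|---|---|
| 2 vs 2 | 0 | 0 | 0% |
| 3 vs 1 | 2/45 × 10 = 0.44 | 2/45 × 20 = 0.89 | 9% to 18% |
| 4 vs 1 | 3/45 × 10 = 0.67 | 3/45 × 20 = 1.33 | 13% to 27% |

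An excess in the placebo arm hides benefit; an excess in the PRP arm hides harm.

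A second illustration supposes that PRP acts only through complications, with D of 5 to 15 points. At assumed rates of 10% on placebo and 5% on PRP, the difference in all randomised patients is 0.05 × 5 = 0.25 to 0.05 × 15 = 0.75 points. At 10% and 2% it is 0.08 × 5 = 0.4 to 0.08 × 15 = 1.2. The analysis after removal shows 0 in both cases.

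**5. Price of keeping these patients.** Assume 7.8 is the SD in patients without complications (its source is not given) and 2 of 45 per arm have a complication. The added variance is (2/45) × (43/45) × D², which is 4.2 for D = 10 and 17.0 for D = 20. The SD becomes √(60.84 + 4.25) = 8.1 or √(60.84 + 16.99) = 8.8. Power at 45 per arm for 5 points is then 82.8% or 75.8%, against 83.6% for 43 per arm after removal at SD 7.8.

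**The case against.** Five points can be made for the plan.

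- **Harms are not shown to be deleted.** A reader might infer that the trial discards its safety events. The text does not support that. Reoperations are recorded, wound healing is examined, radiographs are taken and safety is a named objective. An article may also leave the definition of a safety population to the full protocol or SAP. What stands is narrower: the removal is stated without exempting safety.
- **Not every removed event can depend on treatment.** The injection follows the repair, so an earlier intraoperative fracture cannot be caused or prevented by PRP. The article also states no mechanism by which PRP would alter fracture risk. This stands and limits the bias to later events.
- **Blinding.** Surgeon and patient are blinded and the syringes are taped, which limits arm-dependent judgement about whom to remove. It gives no protection if PRP truly changes how often the events occur.
- **The size is assumed.** This stands. Equal removals with equal deficits give no distortion, and the plausible OHS effect is modest.
- **The ten patients above 80.** A reader might infer that each removal uses up a planned reserve. The article does not explain the gap between 90 and 80. If it is an allowance for losses, using it is no defect: 40 per arm still gives 80.8%.

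None of this turns the rule into an omission that a SAP could fill. It is stated, and a SAP would have to follow it or contradict it.

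**Conclusion.** The rule is wrong as written and should be changed. It excludes patients on an event that, when postoperative, follows randomisation and belongs to the process PRP is meant to influence. The remaining groups are therefore not the randomised groups for OHS, strength or MRI.

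On assumed inputs (45 per arm, 10 to 20 point deficit), the OHS distortion runs from 0 with equal removals to about 0.4 to 1.3 points with an imbalance of 2 to 3 patients, or up to 27% of the 5-point target. Its sign cannot be known beforehand. The case for change therefore rests on the integrity of the comparison and on the exposed safety comparison, not on a demonstrated large bias.

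The documents do not support saying that harms go unrecorded, or that every removed event biases the result.

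**What to change.** Replace the sentence with:

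> All patients for whom an envelope is opened are analysed in the arm assigned, whatever complications follow. Trochanteric fracture, infection and reoperation are reported by arm as safety outcomes in all randomised patients.

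Three additions complete it:

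- Patients withdrawn before the envelope is opened count as not randomised.
- OHS, strength or MRI values missing after a complication are handled by the trial's missing-data method, not by dropping the patient. Otherwise part of the same selection returns.
- The analysis without complicated cases is kept only as a labelled sensitivity analysis.

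The cost is a short text change. The visits at 3 and 12 months are already planned, and the calculated 40 per group does not change. The downside is that retained cases may raise the OHS SD: slightly at a 10-point deficit, and more (to about 8.8 in the illustration above) at 20 points.
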